### Sample size

Two categories of individuals will be identified in each PSU: 1) women with one or more children aged 29 days to 6 months and 2) women with one or more children aged 12–23 months. The sample size for each category was estimated with respect to differences in coverage of two key MNCH services (institutional delivery and full immunization coverage) and neonatal and child morbidity rate for severe disease. For mothers with children in the younger age group, neonatal and child morbidity rates and institutional delivery coverage were used to determine sample size. For mothers with children in the older age group, the difference in rates of full immunization coverage was used to assess sample size.

We determined the sample size required to detect a 5% change in the coverage of MNCH services and neonatal and child morbidity rates, with a power of 80% and an alpha error of 5%. Baseline coverage of 15.1% and 30.8% for institutional delivery and full immunization coverage in control area, respectively, was assumed (18). Similarly, a neonatal morbidity rate of 18.9% for severe neonatal disease was assumed in the control area (4). With these parameters, sample sizes of 1,053 women with a child in the younger age group and 1,391 women with a child in the older age group from the intervention and control areas, respectively, were considered appropriate.

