## Introduction

Globally, maternal and child mortality is declining, although the pace of decline is not sufficient to attain Millennium Development Goals (MDGs) 4 and 5 in almost 128 out of 137 developing countries (1). Significant progress has been made in India for maternal and child health survival. The maternal mortality rate has decreased from 487 to 190 maternal deaths per 100,000 live births between 1990 and 2013 (2). In terms of child mortality, since 1990, the under-five mortality rate has decreased from 126 to 53 deaths per 1,000 live births during the same period (2). Nearly two-thirds of maternal and child deaths in India are contributed by a few states including Assam, Uttar Pradesh (UP), Uttarakhand, Rajasthan, Madhya Pradesh, Chhattisgarh, Bihar, Jharkhand, and Odisha (3). Not surprisingly, the coverage of key maternal, neonatal and child health (MNCH) services in these states is very low. For instance in UP, the coverage of institutional deliveries, full antenatal care (ANC), and full immunization were 45.6%, 29.6%, 45.3%, respectively, in 2011–12 (4).

Since the introduction of the National Rural Health Mission (NRHM) in India in 2005, a number of interventions have been introduced to bolster the coverage of services such as institutional delivery, immunization, and antenatal and postnatal care (5). While NRHM focused on the supply side through strengthening of the government health care system, it also initiated steps to generate demand through community mobilization by creation of a new cadre of community health workers called accredited social health activists (ASHAs) (5). ASHAs act as village-level grass roots workers to generate demand for services. Harnessed properly, this vast pool of human resources can be a potent asset in the Indian government health system. An evaluation of ASHAs in 2011 found that although a 23-day training schedule has been developed by the Ministry of Health and Family Welfare, the quality of training needs to be strengthened in order to improve the performance of ASHAs (6).

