Additionally, mothers in both categories will be interviewed in the intervention and control area about the extent and quality of services offered by the ASHAs during the antenatal and postnatal home visits. Specific questions will be posed to mothers in the intervention area to assess the usage of the mobile application and their satisfaction with this mobile-assisted counseling.

### 
Data analysis

DID will be the primary analysis and will be based on the AHS and CEAHH data from intervention and control areas. Propensity scores will be used to match the women of intervention area with control area based on their socio-demographic characteristics. This will help to reduce the selection bias by taking into account the variation caused by known confounders. The AHS dataset for analysis comprises a total of 450 women: 225 from the intervention areas and 225 from the control areas. The CEAHH data have 1,053 women with a child aged 1–6 months each in intervention and control area. Similarly, a total of 1,391 women with a child aged 12–23 months in intervention and control area are part of the CEAHH dataset.

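### The stated 80% power for a 5-point change fits a 2015-only comparison; the primary difference-in-differences, with 225 baseline women per area, has at best about 19–26% power (two-sided 5% test)

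*Protocol article*

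**What the plan says.** The Sample size section sets the target: "We determined the sample size required to detect a 5% change in the coverage of MNCH services" and in neonatal and child morbidity, with 80% power and 5% alpha. The inputs are single control-area rates: "Baseline coverage of 15.1% and 30.8% for institutional delivery and full immunization coverage in control area, respectively, was assumed", and "a neonatal morbidity rate of 18.9% for severe neonatal disease was assumed in the control area". The result is "sample sizes of 1,053 women with a child in the younger age group and 1,391 women with a child in the older age group", for the intervention and control areas. No baseline-survey sample size enters this calculation.

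The Data analysis section then names the primary analysis: "DID will be the primary analysis and will be based on the AHS and CEAHH data from intervention and control areas". It also fixes the 2011 data: "The AHS dataset for analysis comprises a total of 450 women: 225 from the intervention areas and 225 from the control areas". Part (b) of that section defines DID as the pre–post change in the intervention area minus the pre–post change in the control area. The article gives no power or detectable effect for that contrast.

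**The concern.** The power statement and the primary estimator do not match. A comparison of two areas in one survey has two sources of sampling error. A DID built on two separate cross-sectional surveys has four, and here the two baseline cells are far smaller than the 2015 cells. If 80% power is taken to describe the primary analysis, readers will expect a 5-point gain to be found four times in five, when it would usually be missed. The estimates passed to the cost-effectiveness model would also be much less precise than the sample-size section suggests.

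**Working it through.** **Inputs.** From Sample size: control-area rates of 15.1% (institutional delivery), 18.9% (severe neonatal morbidity) and 30.8% (full immunization); effect 5%, read as absolute points; power 80%; alpha 5%, taken as two-sided because that reproduces the stated sizes. From Data analysis: 225 women per area in 2011. From both sections: 1,053 (younger group) and 1,391 (older group) in 2015, taken per area.

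**Step 1: reproduce the article's figures.** Two proportions, unpooled variance, n per area = (1.96 + 0.8416)² × [p0(1−p0) + p1(1−p1)] / 0.05², where the squared term is 7.849.
- 18.9% vs 23.9%: 7.849 × (0.15328 + 0.18188) / 0.0025 = 1,052.3, so 1,053.
- 30.8% vs 35.8%: 7.849 × (0.21314 + 0.22984) / 0.0025 = 1,390.7, so 1,391.
- 15.1% vs 20.1%: 7.849 × (0.12820 + 0.16060) / 0.0025 = 906.7, so 907. Morbidity therefore drives the 1,053.

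The stated sizes are exactly those of a comparison at a single time point, per area.

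**Step 2: variance of the DID.** Take the four cells as independent, the three untreated cells at p0 and the treated 2015 cell at p1 = p0 + 0.05:

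Var = 2·p0(1−p0)/225 + [p0(1−p0) + p1(1−p1)]/n2015

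Power = Φ(0.05/SE − 1.96). Effect detectable with 80% power = 2.8016 × SE. Floor with an unlimited 2015 sample = 2.8016 × √(2011 part).

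| | Institutional delivery | Severe neonatal morbidity | Full immunization |
|---|---|---|---|
| 2011 part | 0.001140 | 0.001362 | 0.001895 |
| 2015 part | 0.000274 | 0.000318 | 0.000318 |
| 2011 share | 81% | 81% | 86% |
| SE (points) | 3.76 | 4.10 | 4.70 |
| Power for 5 points | 26% | 23% | 19% |
| Detectable effect (points) | 10.5 | 11.5 | 13.2 |
| Floor (points) | 9.5 | 10.3 | 12.2 |

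Immunization power is 18.5%, or 18.6% counting both tails. For a fall in morbidity rather than a rise, power is 23.6%.

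**Step 3: what 80% power would need.** The SE would have to be 0.05/2.8016 = 1.78 points, a variance of 0.000319. For morbidity and immunization the 2015 cells alone (0.000318) use up practically all of that, so the gap does not come from the baseline alone. With equal cells, the DID would need about 1,712, 2,015 and 2,730 women per area per period for institutional delivery, morbidity and immunization.

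**Step 4: other assumptions.**
- Half of the 225 women usable for each outcome (112 per area, an assumption): power 12–17%; detectable effects 14.2, 15.5 and 18.0 points.
- Design effect of 1.5–2 (an assumption; villages are the sampling units in 2015): power 11–19%.
- Common secular rise of 10–30 points: power 18–25%.
- One-sided 5% test: power 28–38%.

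None comes near 80%.

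**The case against.** The best defence is that the Sample size section never says the 80% refers to the DID. It sizes the 2015 survey, the only sample the investigators could choose, and its arithmetic is correct. That stands as far as it goes: the fault is a mismatch with the primary analysis, not a miscalculation. But the article names no other primary analysis and itself gives the baseline cell sizes, so a reader will attach the power claim to the DID.

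The Data analysis section can be read as giving 1,391 for both areas together. Step 1 shows that the figure is per area; read as a total (about 695 per area), immunization power falls to about 17%. Propensity score matching is presented as a way to reduce bias, and no gain in precision is claimed for it.

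Three stronger readings are tempting and should be resisted.
- A reader might infer that a non-significant DID would enter the DALY model as no effect. No section makes significance a condition for modelling. The Discussion says, for the postnatal and neonatal outcomes, that the differences found will be modelled, and no other rule is set for the main outcomes. The supported harm is imprecision carried into the model.
- A reader might infer that interval-based reporting is absent. The Data analysis section already promises effect sizes with confidence intervals for every primary and secondary outcome.
- A reader might apply the 45.6% institutional delivery figure from the Introduction as the 2015 rate. It is a state-wide figure for 2011–12, and nothing in the article shows that the study blocks had reached it by 2015. The choice of baseline rate is a separate question.

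**Conclusion.** The point holds. The stated 80% power for 5 points is a property of a 2015-only contrast, and the primary DID does not have it. The 26%, 23% and 19% are best-case values for a two-sided 5% test. They rest on reading 5% as absolute points, simple random sampling, independent cells, all 225 women per area contributing to each outcome, baseline cells at the assumed control-area rates, no secular trend and no loss from matching. They should not be quoted as the study's actual power, because village clustering, matching losses or a split of the 450 women between outcomes would lower them. The direction does not depend on these choices: the highest power under any variant checked is 38%, with a one-sided test.

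**What to change.** In the Sample size section, state that 1,053 and 1,391 per area give 80% power for a 5-point difference in the 2015 cross-sectional comparison only. Add the DID power and the effect detectable with 80% power, computed from all four cell sizes and using the number of 2011 women who actually feed each outcome. State that number for each outcome, and allow for clustering. The 10.5, 11.5 and 13.2 points above illustrate the best case and should not be copied in as final values. Beside the confidence intervals already promised, add one sentence that a non-significant DID is not evidence of no effect.

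This costs a short recalculation and some rewording. It needs no extra interviews and no change to the analysis. The only downside is a less favourable stated detectable difference.

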### Overview of study design

The study has been approved by the Institute Ethics Committee of the Post Graduate Institute of Medical Education and Research, Chandigarh, India. Written informed consent will be obtained from all study participants. Administrative approval will be obtained for collection of relevant data.

We will use a quasi-experimental design comprising pre- and post-intervention observations with a control to assess the impact of the ReMiND project. Data from the Annual Household Survey (AHS) undertaken by the Registrar General of India in district Kaushambi in 2011 will be used for baseline or pre-intervention assessment (4). The AHS is the largest demographic survey in the world and covers two and a half times that of the Sample Registration System (India's most regular source of demographic statistics). The sampling design adopted for the AHS is a uni-stage stratified simple random sample without replacement, except in case of larger villages in rural areas (i.e. having a population greater than or equal to 2000 as per 2001 census), wherein a two-stage stratified sampling procedure has been applied. The details of the AHS survey are incorporated in the supplementary material.

We will undertake a cost-effectiveness analysis household (CEAHH) survey in 2015 in two intervention blocks and two control blocks from the Kaushambi district to assess the coverage of various MNCH services that represent the post-intervention status. To carry out the CEAHH survey, two structured interview schedules were developed after an extensive review of existing tools used in AHS, the National Family Health Survey, the District Level Household Survey, and the Coverage Evaluation Survey.

Together, the AHS and the CEAHH will be used to assess the impact of the ReMiND m-health intervention using a difference in differences (DID) analysis. To reduce selection bias, before DID is performed, propensity score matching (PSM) will be used to match the cases from the intervention blocks with those in the control group based on their socio-demographic characteristics, for the period between 2011 and 2015 (4). Further, subgroup analysis will be done to analyze the impact of intervention among various levels of underlying factors, such as the mother's education and the occupation of the head of household.

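### The stated 80% power for a 5-point change rests on unprojected baseline coverage in a two-group formula; the planned difference-in-differences with 225 baseline women per area has about 26% (delivery) and 18% (immunization)

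*Protocol article*

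**What the plan says.** The Sample size section describes the "sample size required to detect a 5% change in the coverage of MNCH services and neonatal and child morbidity rates", at 80% power and 5% alpha. For coverage it states: "Baseline coverage of 15.1% and 30.8% for institutional delivery and full immunization coverage in control area, respectively, was assumed", citing reference 18. A control-area rate of 18.9% for severe neonatal disease is also assumed, citing reference 4. The result is "sample sizes of 1,053 women with a child in the younger age group and 1,391 women with a child in the older age group".

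Other sections bear on this:

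- Overview of study design: the 2011 AHS data, cited to reference 4, "will be used for baseline or pre-intervention assessment". The household survey that supplies the post-intervention data takes place in 2015.
- Introduction, also citing reference 4: state coverage of institutional delivery, full antenatal care and "full immunization were 45.6%, 29.6%, 45.3%, respectively, in 2011–12".
- Data analysis: difference in differences (DID) on both surveys is the primary analysis. The AHS dataset has 225 women per area. The 2015 survey has 1,053 younger-group women in each area, and I read 1,391 as per area too.
- Theory of change and Discussion: the district is described as performing worse than the state.

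**The concern.** A power statement should describe the analysis that will be run, at the event rates expected when the data are collected. This one departs from that in two ways.

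First, the coverage rates are baseline rates, used as if control coverage would be unchanged in 2015. The article describes continuing national efforts to raise these services, and it chose DID, a method that allows control areas to move. For a fixed 5-point difference, the variance, and so the required sample, grows as coverage rises toward 50%. The coverage rates also carry a different reference number from the AHS baseline, and the article does not explain the choice.

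Second, the formula is a comparison of two groups at one time. The primary estimate subtracts a baseline difference that is itself estimated from 225 women per area, and that uncertainty is not counted.

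At stake is the reading of the result. A null finding on delivery or immunization could be taken as evidence against a 5-point effect when the study had little chance of detecting one.

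**Working it through.** **1. Reproducing the plan's figures.** Two independent proportions, two-sided 5%, 80% power, 1:1, unpooled variance (the article does not state sidedness or formula):

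n per area = (1.960 + 0.842)² × [p₁(1−p₁) + p₂(1−p₂)] / 0.05², with the squared term equal to 7.849 before rounding.

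- Immunization, 30.8% to 35.8%: 7.849 × (0.2131 + 0.2298) / 0.0025 = 1,390.7, so 1,391. Matches.
- Morbidity, 18.9% to 23.9%: 7.849 × (0.1533 + 0.1819) / 0.0025 = 1,052.2, so 1,053. Matches.
- Delivery, 15.1% to 20.1%: 7.849 × (0.1282 + 0.1606) / 0.0025 = 906.7, so 907.

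So 5% means 5 percentage points. The 1,053 was set by the morbidity rate, not by delivery. Neither figure contains any inflation for clustering or for a baseline survey.

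**2. Two-group power if 2015 control coverage differs.** Power = Φ(0.05/SE − 1.960), with SE² = [p(1−p) + (p+0.05)(0.95−p)]/n.

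| Outcome, n per area | Control coverage in 2015 | Power | n needed for 80% |
|---|---|---|---|
| Delivery, 1,053 | 15.1% (plan) | 86% | 907 |
| | 18.9% | 80% | 1,053 |
| | 25% | 73% | 1,248 |
| | 45.6% (state) | 63% | 1,564 |
| Immunization, 1,391 | 30.8% (plan) | 80% | 1,391 |
| | 40% | 76% | 1,531 |
| | 45.3% (state) | 75% | 1,563 |

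A pooled-variance formula changes these by less than one percentage point. A rise of 3.8 points (18.9 − 15.1) uses up the surplus for delivery. Immunization has none.

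**3. Power of the planned DID at the plan's own rates.** Assumptions: independent simple random samples, equal baseline coverage in both areas, control coverage flat, all 225 AHS women per area contributing to each outcome, and a 5-point gain in the intervention area.

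SE² = 2 × p(1−p)/225 + p(1−p)/n + (p+0.05)(0.95−p)/n

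- Delivery, p = 0.151, n = 1,053: 0.001140 + 0.000122 + 0.000153 = 0.001414, so SE = 0.0376. Power = Φ(0.05/0.0376 − 1.960) = Φ(−0.63) = 26%.
- Immunization, p = 0.308, n = 1,391: 0.001895 + 0.000153 + 0.000165 = 0.002213, so SE = 0.0470. Power = Φ(0.05/0.0470 − 1.960) = Φ(−0.90) = 18%.

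The difference detectable with 80% power, holding these SEs fixed, is 2.802 × 0.0376 = 10.5 points for delivery and 2.802 × 0.0470 = 13.2 points for immunization.

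The baseline term is 0.001140/0.001414 = 81% of the variance for delivery and 0.001895/0.002213 = 86% for immunization. With an unlimited 2015 sample the detectable differences would still be 2.802 × √0.001140 = 9.5 points and 2.802 × √0.001895 = 12.2 points. Interviewing more women in 2015 would therefore not restore the claim.

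**4. Clustering.** No design effect is stated for the 69 villages per area. In the two-group formula, one above 1,053/907 = 1.16 removes the delivery surplus. With about 1,053/69 = 15.3 women per village and equal takes, an intracluster correlation of 0.16/14.3 = 0.011 gives that design effect. The documents give no correlation, so this shows sensitivity only.

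**The case against.** Four arguments on the other side have weight.

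- **The source.** A reader might infer that 15.1% and 30.8% come from a survey other than the AHS. The reference list is not shown. Only the citation number differs, so the documents do not support that inference.
- **The state average.** A reader might take 45.6% and 45.3% as contradicting the assumed rates. They do not. The assumed rates are for the control area, and the article says repeatedly that the district does worse than the state. No local AHS coverage figure is given. The state values mark an upper illustration, and the immunization loss is modest even there.
- **The 18.9% crossing point.** A reader might conclude that 80% power is safe while control delivery coverage stays below about 19%. It is not. That threshold belongs to the two-group formula and arises because morbidity set the sample size. The DID falls far short even at 15.1%.
- **Reporting and remedy.** The Data analysis section promises effect sizes with confidence intervals, so a null result would be shown with its precision. That limits the harm but leaves the planning claim wrong. It is also fair that 225 women fix a 15.1% rate only to about ±1.96 × √(0.1282/225) = ±4.7 points, so a single recalculated figure would be fragile. A range is needed, and it must be for the DID.

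**Conclusion.** The point holds, and it is about the power claim rather than a wrong input. The stated 80% belongs to a one-time two-group comparison at unprojected baseline rates, and the planned primary analysis does not deliver it. At the plan's own rates the DID has about 26% power for delivery and 18% for immunization, and can detect about 10.5 and 13 points rather than 5. These figures rest on simple random sampling, flat control coverage, equal baselines and all 225 women per area contributing. Clustering would be expected to lower them further.

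The dependence on 2015 control coverage is a secondary and conditional part. Within the two-group formula, delivery power runs from 86% at 15.1% to 63% at the state level, and immunization power from 80% to 75%. Where the control blocks will fall is not in the documents. The documents do not show that 15.1% or 30.8% is incorrect for these blocks.

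**What to change.** Keep 1,053 and 1,391. Recompute power for the DID, taking 2011 coverage in the four selected blocks from the AHS dataset the article already describes, and a stated range for 2015 control coverage (for example 15% to 46% for delivery and 31% to 45% for immunization). Include the 225-per-area baseline, with the number of AHS women who actually contribute to each outcome, and a stated allowance for village clustering. Replace the 80% claim with the resulting power or minimum detectable difference for each outcome. Say in a sentence why the coverage rates carry a different reference from the baseline survey.

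No additional women are needed. The cost is one recalculation and a less favourable stated figure, which is also the figure a reader needs to interpret a null result.

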### Sampling

The primary sampling unit (PSU) for the CEAHH survey will be a village. For selection of PSUs, a list of all villages from the two intervention and two control blocks will be prepared. From all villages in Kaushambi, 10% of each will be selected from the intervention area and the control area. This means that 69 PSUs each will be selected randomly from the intervention and control areas, using the probability proportional to size method.

In each PSU, a household enumeration will be undertaken to identify all mothers with a child in the age group of 29 days to 6 months, or between 12 and 23 months on the date of the survey. This list will serve as the sampling framework to randomly select the required number of mothers in each category for interview. The number of clients to be interviewed per PSU will again be selected by the probability proportional to size method and will be determined based on the relative size of the PSU.

The clients (mothers with a child in the 29 days to 6-month or 12- to 23-month age range) within each PSU will be selected using systematic random sampling. If more than one child in the respective age category is present in a given household (i.e. more than one child is between 29 days and 6 months or more than one child is between 12 and 23 months), then one will be randomly selected. If the family has one child in the 29 days- to 6-month range and one in the 12- to 23-month range, then both children would be part of the sampling frame and would have the same probability of being selected as would any other child in the sampling frame.

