(a) PSM: The non-random choice of the two intervention blocks could result in selection bias. In order to minimize this bias, the PSM method will be used to control for demand-side characteristics that could influence utilization of various MNCH services. The PSM approach attempts to render the effects of different observed covariates X on participation as a single propensity score or index defined byP(X)=Pr(T=1∣X).The idea is to find, from a large group of control area women, those who are observationally similar to the intervention area women in terms of characteristics that are unaffected by the m-health intervention but that influence the utilization of key MNCH services (25). Then, each woman in the intervention arm will be matched with a woman in the control arm who is observationally similar (e.g. on socio-economic characteristics like literacy rate, caste, occupation of the mother, and age). The PSM estimator for the treatment effect on the treated can be specified as the mean difference of Y (i.e. institutional delivery or full immunization, or any other key indicator under consideration) over the usual support, weighting the comparison units by the propensity score distribution of eligible women in the respective categories. A typical cross-section estimator can be specified as follows:$$TOT_{PSM}=E_{P(x)|T=1}\{E[Y^{T}|T=1,P(X)]-E[Y^{C}|T=0,P(X)]\}.$$

(b) DID: This method essentially compares intervention and control groups in terms of outcome changes over time relative to the outcomes observed for a pre-intervention baseline. That is, given a two-period setting where *t*=0 before the program and *t*=1 after program implementation, letting $Y_{t}^{T}$ and $Y_{t}^{C}$ be the respective outcomes for a program beneficiary and non-treated units in time *t*, the DID method will estimate the average program impact as follows:$$DID=E(Y_{1}^{T}-Y_{0}^{T}|T_{1}=1)-E(Y_{1}^{C}-Y_{0}^{C}|T_{1}=0)$$In equation (1), *T*_1_=1 denotes treatment or the presence of the program at *t*=1, which is evaluated from CEAHH data, whereas *T*_1_=0 denotes absence of the program, which is evaluated using AHS data. Outcomes in the form of coverage of key MNCH services such as ANC, immunization and institutional deliveries will be assessed (25). Along with the above techniques, for each primary and secondary outcome, the estimated effect size and confidence intervals will be estimated to indicate the levels of precision.

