In the context of the present study, the intervention is to be rolled out in two blocks in the district. This offers distinct benefits for evaluating the impact. However, the choice of the two intervention blocks was not random, and this selection bias can limit the causal attribution if inherent differences in the two intervention blocks versus the remaining six control blocks of the district influence the outcome. However, we will attempt to account for this in our analysis, where the demand-side factors at household level will be controlled using PSM, and the supply-side health system factors other than m-health application are controlled using the DID estimator.

Second, the intervention involves use of mobile phones to deliver health messages and counseling. Given the nature of the intervention, it is not possible to blind the participants. Also since specific questions pertaining to the use of intervention are included in the structured questionnaire on delivery of intervention, the investigators who assess outcomes also cannot be blinded to the intervention.

Third, we aim to assess provision of home-based postnatal care through ASHAs, morbidity and care seeking during the neonatal and infancy periods. We note that these were not the primary objective of ReMiND, as its m-health application was limited to being a job aid for ANC, institutional delivery, and immunization. However, since the m-health application might affect the performance of ASHAs and their contact with the women during pregnancy, it is likely to have spin-off effects during the postnatal period. Whatever differences accrue for neonatal care seeking, postnatal care, and so on, the same differences will be modeled as health gains in the form of DALY averted. Moreover, the baseline survey elicited data on provision and quality of ASHA visits during the postnatal period, neonatal morbidity and care seeking. Hence, it is feasible to assess impact, if any.

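### The sample sizes assume independent women although the survey samples villages, so the stated 80% power is overstated by an amount that depends on an unstated intracluster correlation

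*Protocol article*

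**What the plan says.** All references are to the protocol article.

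- **Sample size.** The aim is to "detect a 5% change in the coverage of MNCH services and neonatal and child morbidity rates" at 80% power and 5% alpha. The control-area inputs are: "Baseline coverage of 15.1% and 30.8% for institutional delivery and full immunization coverage in control area, respectively, was assumed", and "a neonatal morbidity rate of 18.9% for severe neonatal disease was assumed in the control area". The result follows directly: "With these parameters, sample sizes of 1,053 women with a child in the younger age group and 1,391 women" for the older group. No ICC, design effect or other inflation appears.
- **Sampling.** The village is the primary sampling unit, and "69 PSUs each will be selected randomly from the intervention and control areas, using the probability proportional to size method". Several mothers are then interviewed in each village.
- **Data analysis.** DID is the primary analysis, after woman-to-woman propensity score matching. For each outcome "the estimated effect size and confidence intervals will be estimated to indicate the levels of precision". No variance method is named.
- **Study setting, Study area and Discussion.** The application was introduced in two whole blocks, not chosen at random, and two other blocks serve as controls. The Discussion says that "the supply-side health system factors other than m-health application are controlled using the DID estimator".

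**The concern.** The Sample size section calculates for a simple random sample, and the Sampling section describes a cluster sample. Women in one village share facilities and, because the Introduction describes ASHAs as village-level workers, largely the same worker through whom the intervention acts. Their outcomes are likely to be positively correlated. If so, 1,053 and 1,391 women carry less information than the same number of independent women, and a null result could be read as adequately powered when it was not.

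Two related matters follow. If the same independence assumption entered the analysis, the intervals would be too narrow. And the Discussion credits DID with more than it can do: it removes differences between areas that are constant over time and changes common to both areas. A supply-side change between 2011 and 2015 that differed between the areas stays in the estimate. With two blocks against two, interviewing more women or villages does not shrink that component.

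**Working it through.** **Inputs from the article.** Control rates 18.9% (severe neonatal morbidity), 30.8% (full immunization) and 15.1% (institutional delivery); difference 5 percentage points; power 80%; alpha 5%; 69 villages per area. The article does not state sidedness; a two-sided test reproduces its figures.

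**Step 1: reproduce the stated sizes.** For two independent proportions with unpooled variance, n per area = (1.960 + 0.842)² × V / 0.05², where V = p₁(1−p₁) + p₂(1−p₂).

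- Morbidity, 18.9% v 23.9%: V = 0.1533 + 0.1819 = 0.3352; n = 1,052.2, rounded up to 1,053.
- Full immunization, 30.8% v 35.8%: V = 0.2131 + 0.2298 = 0.4430; n = 1,390.7, rounded up to 1,391.
- Institutional delivery, 15.1% v 20.1%: V = 0.1282 + 0.1606 = 0.2888; n = 906.7, rounded up to 907.

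Morbidity sets the younger-group size and immunization the older-group size. Both match the article exactly, so nothing was added for clustering. The match also shows that 1,391 is a per-area figure.

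**Step 2: design effect.** Mean women per village: m = 1,053/69 = 15.26 and 1,391/69 = 20.16. DE = 1 + (m − 1) × ICC. The ICC is an assumption, taken over 0.01 to 0.10. Interviews per village vary with village size, so a formula using the mean m tends to understate DE.

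**Step 3: power of the 2015-only comparison.** Power = Φ(0.05 / √(V × DE / n) − 1.96). Example, morbidity at ICC 0.05: DE = 1.713; effective n = 1,053/1.713 = 615; SE = √(0.3352/615) = 0.0233; 0.05/0.0233 − 1.96 = 0.18; power 57%.

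| Assumed ICC | DE, younger | Morbidity | Institutional delivery | DE, older | Full immunization |
|---|---|---|---|---|---|
| 0 | 1.00 | 80.0% | 85.5% | 1.00 | 80.0% |
| 0.01 | 1.14 | 74.6% | 80.6% | 1.19 | 72.8% |
| 0.02 | 1.29 | 69.6% | 75.9% | 1.38 | 66.4% |
| 0.05 | 1.71 | 57.2% | 63.6% | 1.96 | 51.7% |
| 0.10 | 2.43 | 43.6% | 49.1% | 2.92 | 37.5% |

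**Step 4: the same loss as a detectable difference.** With V held at the planned rates, the 5 points become 5 × √DE: 5.3 to 7.8 points for morbidity and 5.5 to 8.5 points for immunization over ICC 0.01 to 0.10.

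**Step 5: what ignoring clustering would do to intervals.** For the 2015 contrast, correct intervals are √DE times as wide: 1.07 to 1.56 (younger) and 1.09 to 1.71 (older). For DID the effect is diluted, because the 2011 sample of 225 women per area dominates the variance. For institutional delivery, assume that all 225 contribute and that both areas start at 15.1%:

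- 2011 term: 2 × 0.1282/225 = 0.00114; 2015 term: 0.2888/1,053 = 0.00027; SE = √0.00141 = 3.8 points.
- Multiplying only the 2015 term by 1.14 to 2.43 gives SE = 3.8 to 4.2 points, that is, 1% to 13% wider.

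Clustering in the Annual Health Survey (AHS) would add to this, but the article gives neither the number of AHS villages nor the women per village.

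**The case against.** **Intervals.** A reader might infer that the planned intervals treat women as independent and are too narrow. The article does not support that. It names no variance method, and an article commonly leaves this to the full protocol or analysis plan. The matching and DID formulas are differences of expectations: they define what is estimated, carry no independence assumption, and are compatible with clustered variance. Only the conditional statement stands. It is also easy to overstate its size by quoting error rates for a naive test of the 2015 contrast, which is not the primary analysis. For DID the widening that can be shown from documented inputs is modest, and a larger figure needs an AHS design effect that the article does not give.

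**Power.** The loss is not uniform. Institutional delivery, a direct target of the application, has slack and still reaches 80% at ICC 0.01. The Discussion says that morbidity was not a primary objective of the project. The morbidity size also reproduces only for a 5-point rise; for a 5-point fall, power at 1,053 is about 87% under independence, 83% at ICC 0.01, 78% at 0.02 and 51% at 0.10. These points soften the loss at very small ICCs. They do not rescue the stated calculation, which rests on the two outcomes without slack.

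**Block-level change.** A reader might infer that a change in one pair of blocks would simply be reported as an effect of the application. The article is more careful: the Discussion concedes that non-random block choice can limit causal attribution, and the Process evaluation section plans to monitor other interventions introduced differentially between the areas. What remains is one overstated clause.

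**Conclusion.** The concern holds for the sample size. The stated sizes are simple-random-sample sizes applied to a survey of 69 villages per area. As calculated, any positive ICC takes the two outcomes that set the sizes below 80% power. The direction is certain for a positive ICC; the size rests on an assumed range of 0.01 to 0.10, over which power is about 75–44% (morbidity), 73–37% (full immunization) and 81–49% (institutional delivery). These figures concern the 2015-only comparison; the calculation was never one for DID.

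That the intervals are too narrow is not established: they would be if clustering were ignored, and the article does not say. The Discussion's sentence on supply-side factors is overstated and needs correcting, as a secondary matter of wording.

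**What to change.** 1. Keep the sample size. Restate the power, or the differences detectable with 80% power, with a stated ICC, its source, and the resulting design effects for about 15 and 20 women per village. If no ICC can be sourced, show a range.
2. State that DID intervals and tests will use village-clustered variance, by survey-design methods or a cluster bootstrap, applying the AHS sampling units where they can be identified.
3. Correct the Discussion to say that DID removes only differences constant over time and changes common to both areas. Qualify attribution by the planned monitoring of other interventions, because two non-randomly chosen blocks are compared with two.

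DID estimates for each pair of blocks could be shown as an optional extra, but they overlap and would be imprecise.

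The cost is wording and analysis code, with no new data. The downside is wider intervals and a less favourable power statement.
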